#### Recruitment

Each leading site will run recruitment for the different population groups separately yet with similar and overlapping strategies. We will recruit English-speaking (mother tongue or fluent) participants globally through our experienced RecMap investigator team (https://covid19.recmap.org/about), the Cochrane Consumer Network and various Cochrane networks, guideline co-authors who interact with youth (including the international Young Persons’ Advisory Groups), parents, and adult citizens. We plan to run public recruitment campaigns through identified youth, adult, and parent organizations’ social media platforms (e.g., organizations’ accounts on Twitter, Instagram, and Facebook) and newsletters. Each leading site will be responsible for monitoring its own recruitment, though all investigators will support overall recruitment for the trials (e.g., if recruitment falls behind for one of the populations, other sites will help support recruitment for that group). Surveys will be administered through SurveyMonkey, where participants are screened for eligibility prior to allocation. Previous studies suggest that the target recruitment rates for such trials are achievable in less than 3 months, and we will recruit at least 240 participants per group [18–20].

The average survey completion time is estimated to be 15–25 min, based on stakeholder feedback and pilot testing. As suggested by our stakeholders in the preparation of this trial, we will be inviting participants who complete the survey to enter a draw for a chance to win one of five $50 CAD gift cards for the adult and parents’ populations. The youth group will invite youth participants to enter a draw for one of ten gift cards valued at $25 CAD. This is offered as a gesture and appreciation for completing the survey.

### Intervention and comparison

In these trials, the intervention is the PLR, and the comparison is the SLV. Figure 2 shows an example of the SLV format of a recommendation that will be used with the adult and youth participants, and Fig. 3 shows an example of a PLR format that will be presented to adult participants. Since this is a non-clinical trial, receiving either the intervention or the control will not require alteration to any part of the participant’s life. Additionally, we do not have special criteria for discontinuing or modifying the allocated intervention.

**Fig. 2 Fig2:**
[figure not shown]
SLV format for youth and adult participants

**Fig. 3 Fig3:**
[figure not shown]
Example of a plain language recommendation summary format for adult participants

Through our pre-trial engagement work, we gathered input from youth (via online workshops) and from adult stakeholders (via online meetings) on high-priority COVID-19 topics and on PLR content and format. Input from youth and adult stakeholders allowed us to choose two recommendations for the trials and refine the PLR format. For the parents’ population, the PLRs were refined from collected feedback during online meetings with parent groups.

All PLRs for the trials were developed from the same template and refined using stakeholder feedback. The youth and parent PLRs’ design and formatting are the same, as these groups gave similar feedback, while the adult PLRs are slightly different.

In the trials, we will ask participants to read one format of a recommendation (PLR or SLV) to which they have been randomly allocated and then answer the online survey that takes an average of 15–25 min to complete.

### Outcomes

#### Primary outcome

##### Understanding

We define understanding as the comprehension of key guideline content (e.g., year of publication, intent of recommendation, direction of recommendation, etc.). This outcome will be measured using seven multiple-choice questions about key concepts in the recommendation with four to six response options for each question and only one correct answer (total minimum score of 0, maximum score of 7). Based on previous work, we aim to detect a difference of 10% in understanding between groups which we consider an important difference (an average difference of 1 correct answer) [18, 19, 21–23].

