### Sample size calculation

The sample size was calculated using the primary outcome of understanding. For this two-sided (*α* = 0.05) superiority analysis, these computations were made based on a *t*-test with the null hypothesis that there is no difference between the PLR version and the SLV in understanding of information.*H*_*0*_*:* PLR version = SLV*H*_*1*_*:* PLR version ≠ SLV

We will determine whether we can reject the null hypothesis of no difference in understanding between the formats of presenting recommendations. We assume a correct response rate (regarding the understanding of information) of 75% in the PLR arm and 60% in the control arm [relative risk =1.25] based on a recent RCT and prior trials on plain language summaries (PLS) of summary of findings table [19, 23]. With typical alpha (0.05) and beta (0.8) parameters and an allocation ratio of 1:1, 240 participants (120 in each arm) would be required (Stata/SE 16.0) [27]. Assuming 15% non-completion, we will recruit 282 participants from each population and adjust this number if non-completion is higher.

Since we are using two different recommendation topics with each population, we might observe an interaction between the recommendation topic and our outcome of understanding. Thus, when we reach half of our intended sample size, we will conduct an interim analysis for a possible interaction effect. If the data suggests that there might be an interaction, we will consider modifying our initial sample size. This new sample size cannot be determined in advance since we cannot anticipate the magnitude of the potential interaction effect, but it will be determined based on published guidance on power calculations for credible subgroup effects [28]. If needed, we will submit an amendment that explains the new sample size and need for additional recruitment based on the magnitude of the interaction effect identified. In summary, an enhanced sample size, if indicated and feasible, will allow us to conduct a more meaningful analysis by exploring the results by topic of recommendation.

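### The important difference in understanding is given as 10% and as 1 of 7 answers (14.3%), the trial is sized on 15 points, and the power for the stated target is left undetermined

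*Protocol article*

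**What the plan says.** Under Understanding (Primary outcome), the Protocol article describes seven multiple-choice questions, each with one correct answer, giving a "total minimum score of 0, maximum score of 7". It then says "we aim to detect a difference of 10% in understanding between groups which we consider an important difference (an average difference of 1 correct answer", the words in brackets being its explanation of the 10%. It does not say whether the 10% is absolute or relative.

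Under Sample size calculation, the planning values are "75% in the PLR arm and 60% in the control arm", a relative risk of 1.25. The section names a t-test but gives proportions and no SD. The error rates are introduced by "For this two-sided (*α* = 0.05) superiority analysis" and "With typical alpha (0.05) and beta (0.8) parameters"; the 0.8 can only sensibly be read as power. The result is 240 participants, 120 per arm, in each population.

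Under Inferential analysis, understanding is to be compared by a chi-square test and a risk difference on the proportion of correct responses. Nothing connects the 10% in the outcome definition with the 15 points in the sample size.

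**The concern.** The sentence that fixes the important difference for the primary outcome treats two unequal quantities as equal. It also says the trial aims to detect 10%, while the sample size rests on a larger difference.

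Two things are at stake:

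- **Interpretation.** This is the only threshold of importance in the article. An observed difference of 0.8 items (0.8/7 = 11.4%) is important if the threshold is 10% and not important if it is one answer. That choice could be made after the results are seen, in each of three trials and in the meta-analysis.
- **Power.** The reader cannot tell what difference 120 per arm can detect, because neither the target nor the unit of analysis (score, or one binary result per participant) is settled.

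**Working it through.** **Inputs from the Protocol article.** Seven items, score 0–7; target 10%, or 1 answer; planning rates 0.75 and 0.60; two-sided 0.05; power 0.80; 120 per arm. **Assumed:** the 10% is absolute; the control rate is 60% throughout; SDs of the score are illustrative, because none is given. All power figures use the normal approximation.

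**Step 1. One scale for all targets.**
- 1 answer = 1/7 = 14.3%.
- 10% = 0.10 × 7 = 0.70 answers.
- 15 points = 0.15 × 7 = 1.05 answers.
- If the 10% were relative to a 60% control rate, it would be 6 points, or 0.06 × 7 = 0.42 answers, which is further from 1.

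**Step 2. The plan's own figure, as two proportions.** With p̄ = 0.675,

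n per arm = [z_α √(2p̄(1−p̄)) + 0.842 √(p₁(1−p₁) + p₂(1−p₂))]² / (p₁−p₂)².

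- Two-sided, z_α = 1.960: 151.9, so 152 per arm (304 in total).
- One-sided, z_α = 1.645: 119.5, so 120 per arm (240 in total).

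The stated 240 is not reproduced with the stated two-sided test. Within this formula it appears only with a one-sided 0.05. The article does not show which route was taken.

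**Step 3. Power of 120 per arm with one binary result per participant.** Power = Φ[(d − 1.960·SE₀)/SE₁], with SE₀ = √(2p̄(1−p̄)/120) and SE₁ = √((p₁(1−p₁) + p₂(1−p₂))/120).

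| Comparison | d | SE₀ | SE₁ | Power | n per arm for 80% |
|---|---|---|---|---|---|
| 70% vs 60% | 0.100 | 0.0616 | 0.0612 | 36.8% | 356 |
| 74.3% vs 60% | 0.143 | 0.0606 | 0.0599 | 65.6% | 169 |
| 75% vs 60% | 0.150 | 0.0605 | 0.0597 | 70.1% | 152 |

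**Step 4. Power of 120 per arm on the 0–7 score by t-test.** Power = Φ[δ/(SD·√(2/120)) − 1.960].

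| Assumed SD (items) | δ = 0.7 items (10%) | δ = 1 item (14.3%) |
|---|---|---|
| 1.25 | 99% | above 99% |
| 1.6 | 92% | above 99% |
| 2.0 | 77% | 97% |
| 2.5 | 58% | 87% |
| 3.3 | 37% | 65% |

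The ends of the SD range come from rates of 60% and 70%. Independent items give √(7 × (0.24 + 0.21)/2) = 1.25. Items that are all right or all wrong together give 7 × √((0.24 + 0.21)/2) = 3.32, the value that gives 37%.

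Power of 80% needs an SD of at most 0.7/(2.802 × √(2/120)) = 1.94 for 0.7 items, and at most 1/(2.802 × √(2/120)) = 2.76 for one item.

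**The case against.** Four points on the other side deserve a fair answer.

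- **The flat 37%.** A reader might infer that the trial simply has 37% power for its stated aim. The article does not support that. It nowhere defines a single binary result per participant: the outcome is a 0–7 score, the sizing names a t-test, and each participant gives seven responses. On the score, 37% arises only when the seven items are fully correlated. It is the worst case, and this objection stands. The binary reading is still a fair one, because the sample size is built from proportions and the planned test is a chi-square, but it is conditional.
- **Three incompatible targets.** A reader might infer this as well. It goes too far: one answer and 15 points differ by 0.05 of an item, and an expected effect taken from earlier trials may properly exceed a minimal important difference. The firm contradiction is 10% against one answer. Alongside it, the article says it aims to detect 10% but sizes on 15 points and does not explain the link.
- **Harm to inference.** Neither the 10% nor the one answer is a decision rule. The analysis uses p < 0.05 and a risk difference with a 95% confidence interval, and the interval will show what is excluded. Nothing says a null result would be read as ruling out 10%. This stands: the test is not invalidated, and the damage is to interpretation and to the power claim.
- **No extra participants needed.** This cannot be promised. It holds on the score if the SD is small enough. It does not hold on the binary calculation, which needs 356 per arm for 10 points.

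**Conclusion.** The point holds in this form. The important difference for the primary outcome is wrong as written: 10% and one answer of seven are equated although they differ by 0.3 of an item. The sample size uses 15 points without relating this to the 10% the trial aims to detect.

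The consequence for power is conditional. With one binary result per participant, a 60% control rate and two-sided 0.05, 120 per arm gives about 37%, 66% and 70% for 10, 14.3 and 15 points, so the stated 80% is not met for any of them. On the 0–7 score, power for 0.7 items runs from about 99% to 37% over assumed SDs of 1.25 to 3.3, and the article gives no SD that would narrow this. The article therefore supports neither the claim that the trial is adequately powered for 10% nor the claim that it is not.

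**What to change.** 1. State one important difference in items with its exact percentage, either 0.7 of 7 (10%) or 1 of 7 (14.3%), and say that it is absolute. Use it in the outcome definition, the sample size section and the interpretation.
2. Name the 0–7 score as the unit of analysis, in line with the t-test in the sample size section, and bring the Inferential analysis text into agreement with it.
3. Restate the power of 120 per arm for the chosen difference, with the SD labelled as an assumption and preferably shown over a range as in step 4.
4. If 75% against 60% is kept, describe it as the expected effect, separate from the important difference. Do not claim 80% power for it on the two-sided binary calculation, where it is about 70%.

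The cost is a few sentences, and a stated power that may be less favourable than 80%. Whether more participants are needed can be judged only once the difference, the unit of analysis and the SD are fixed.

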#### Secondary outcomes

##### Accessibility and usability

We define accessibility and usability as the ability to find/access and use the presented information. This outcome considers the three following domains: (1) how easy it was to find information, (2) how easy it was to understand the information (perception), and (3) whether the information was presented in a way that could be helpful for making an informed health decision. Participants will be asked to indicate the degree of agreement with six statements, measured using the 7-point Likert scale (1 being strongly disagree, 4 being neutral, and 7 being strongly agree). We will also include 1 open-ended question to get additional input on accessibility and usability. The outcome “overall accessibility/usability of information” will be measured using the average of the 7-point Likert-type scale questions.

##### Satisfaction 

We define satisfaction as participants’ impression of the recommendation’s presentation. We will ask participants about their level of satisfaction with different features of the format (e.g., order of information, length of document, etc.) [24]. Participants will be asked to indicate the degree of satisfaction with three questions measured using the original 7-point Likert-type scale (1 being very dissatisfied, 4 being neutral, and 7 being very satisfied). We will also include two open-ended questions to get their input on what they liked and disliked in the format.

##### Intended behavior

We define intended behavior as participants’ intention in adopting and following the shared recommendation. We will ask participants if they have already followed the recommendation and have them respond with yes, no, unsure, prefer not to answer, or not applicable. Subsequently, we will ask how likely it is that they will follow the recommendation (if they have not already) and share the recommendation with others, through two questions measured using a 7-point Likert-type scale (1 being very unlikely, 4 being neutral, and 7 being very likely).

##### Preference

We define preference as a greater liking of one format over the other (PLR or SLV). After participants complete the tasks in the group they are randomized to, they will be asked to compare the PLR and the SLV formats. Participants will review the alternative format and indicate their preference for one of the two formats using a 7-point Likert-type scale (1 being strongly preferring the SLV, 4 being the same preference for both, and 7 being strongly preferring PLR). Participants will also have the chance to explain their choice in a text box.

### Stratification

We will stratify our participants by region: Africa, Americas, Eastern Mediterranean, Europe, South-East Asia, and Western Pacific. We have not set a target sample per strata. The rationale behind stratification is to ensure an equal chance for participants from the same region to be randomized to either the intervention or control (as opposed to having all participants from Europe, for example, being randomized to the PLR format).

### Randomization

After stratification, participants will be randomly assigned in a 1:1 ratio to recommendation topic 1 or 2, then will be randomized again in a 1:1 ratio to the PLR or the SLV arms (see Fig. 1). Randomization will ensure that recommendation formats will be equally distributed across participants to get balanced judgments on outcomes.

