#### Selection criteria

In this study, adults are defined as individuals self-reported to be 21 years of age or older, youth are defined as individuals self-reported to be between the ages of 15 and 24 years [17], and parents are defined as individuals self-reported to be 18 years or above and are a parent or legal guardian of a child under 18 years old. Participants can be from any country. For all three populations, participants will need to be able to read and understand English. We expect variation in the English language proficiency and health literacy level among participants. Therefore, when collecting demographic information, questions related to language proficiency and familiarity with COVID-19 health information will be included to understand the participant’s level of health literacy. We may adjust for these variables in our analysis if needed, although we expect them to be reasonably balanced between the SLV and PLR groups due to randomization.

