### Allocation concealment

The allocation sequence is concealed using SurveyMonkey® software based on a commercial, but unknown algorithm without a pre-identified sequence.

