### Consultation and pilot testing

We will use the same survey template for all populations; however, the “understanding” questions will be appropriately different for each recommendation. We pilot tested the surveys during the pre-trial engagement work to gather feedback from Canadian youth advisors, Cochrane Consumer Network, adult stakeholders, and parent stakeholders. We had 10 youth, 29 adults, and 5 parents pilot test the survey and provide feedback on the time to complete the survey, length of the survey, clarity of questions, Internet difficulties, and any other comments to enhance the survey experience. Revisions were made to the surveys using pilot test feedback until no errors or inconsistencies were detected and the surveys were easily understood. The survey language used for each population is tailored based on the feedback from stakeholders. Pilot test participant results will not be included in the final analysis.

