#### Inferential analysis

We will perform a primary analysis including all randomized participants. We will exclude participants who take less than 6 min to complete the survey. For the outcome of understanding, we will use *χ*^2^ tests and risk difference with 95% CIs to compare the proportion of correct responses between groups. For the outcomes of accessibility and satisfaction, we will use *t*-tests and mean differences 95% confidence intervals (95% CIs) to compare means and SDs between the intervention and control groups. Finally, we will present preference as mean (SD) overall and for both trial arms. Skewness, Shapiro-Wilk tests, and histograms will be used to evaluate whether the distribution was shifted toward the same preference in both groups. Levene’s test of equal variances will be used for all *t*-tests and degrees of freedom will be adjusted for *p* < 0.05. We will report all *p*-values to three decimal places, with values less than 0.001 reported as < 0.001. We will consider statistical significance at *p* < 0.05. Furthermore, we will conduct a meta-analysis across the three trials by combining results of the three trials. Our a priori hypothesis is that there is no difference across the three populations despite the differences in population characteristics and slight difference in the presentation formats for each population. However, we will explore differences between trials applying the GRADE approach to evaluating inconsistency which includes the chi-square test, the *I*^2^ value, the overlap in confidence intervals, and the differences in the point estimates of effect for all outcomes [29].

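### Format is randomised within region and topic, but the primary comparison adjusts for neither and covariate adjustment is left open, so precision may be lost and some discretion remains

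*Protocol article*

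**What the plan says.** On design, the Stratification section of the Protocol article reads: "We will stratify our participants by region: Africa, Americas, Eastern Mediterranean, Europe, South-East Asia, and Western Pacific". It sets no target number per region. The Randomization section adds two steps: "After stratification, participants will be randomly assigned in a 1:1 ratio to recommendation topic 1 or 2", followed by a second 1:1 allocation to format. Consultation and pilot testing says that the understanding "questions will be appropriately different for each recommendation". Allocation concealment describes the SurveyMonkey allocation as "based on a commercial, but unknown algorithm without a pre-identified sequence".

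On analysis, the Inferential analysis section assigns to understanding chi-square "tests and risk difference with 95% CIs to compare the proportion of correct responses between groups", and to accessibility and satisfaction t-tests with mean differences. None of these carries a term for region or topic. Region does not appear in the quantitative analysis sections at all. Topic, health literacy and English proficiency appear under Statistical analysis as subgroups, and topic also in the interim look for an interaction described under Sample size calculation.

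On covariates, Selection criteria says of language proficiency and familiarity with COVID-19 health information (the plan's gauge of health literacy): "We may adjust for these variables in our analysis if needed". It adds that balance between arms is expected. No trigger, model or timing is given.

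**The concern.** The trial builds region and topic into its allocation and then leaves both out of the comparison it will be judged on. Topic is a plausible source of score variation: each topic has its own question set, and the article does not say that the sets were matched for difficulty. The plan takes topic seriously enough to schedule an interim look and a possible change of sample size, but not to put it in the primary analysis.

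Two things are at stake. One is precision: variation between topics and regions stays in the error term. The other is discretion: an optional adjustment with no trigger leaves someone to choose between adjusted and unadjusted results once the data are in.

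**Working it through.** **1. The plan's own figure.** Inputs from Sample size calculation: 75% versus 60%, two-sided 5%, 80% power, 1:1, 240 in total. The pooled two-proportion formula is

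n per arm = [z(α)·√(2·p̄·(1−p̄)) + z(0.80)·√(p₁(1−p₁)+p₂(1−p₂))]² / (p₁−p₂)²

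with p̄ = 0.675, so the roots are √0.43875 = 0.6624 and √0.4275 = 0.6538.

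- Two-sided: (1.960×0.6624 + 0.8416×0.6538)²/0.0225 = 151.9, so 152 per arm, 304 in total.
- One-sided: (1.645×0.6624 + 0.8416×0.6538)²/0.0225 = 119.5, so 120 per arm, 240 in total.

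The stated 240 is reproduced only one-sided. That is a separate matter, but it sets the baseline here: with 120 per arm, two-sided power is about 70% (70.1% on the pooled formula, 71.0% on the unpooled one).

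**2. Size of the groups randomised within.** Six regions × two topics = 12 cells per population. If spread evenly, 240/12 = 20 per cell. With no target per region, some cells will probably be smaller.

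**3. Precision lost by not adjusting.** Adjustment multiplies the variance of the format effect by about (1 − R²), where R² is the share of outcome variance that the adjustment terms explain. The article gives no R², so a range is assumed. Equivalent number = 240 × (1 − R²). Adjusted power = Φ(0.15/(0.0597·√(1−R²)) − 1.960), where 0.0597 = √(0.4275/120).

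| Assumed R² | Adjusted participants giving the same information as 240 unadjusted | Two-sided power of 240 if adjusted (71% unadjusted) |
|---|---|---|
| 0.02 | 235 | 72% |
| 0.05 | 228 | 73% |
| 0.10 | 216 | 75% |
| 0.20 | 192 | 80% |
| 0.30 | 168 | 85% |

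To place topic alone on this scale: if the question sets differ by d items in difficulty and the within-topic SD is 1.7 (both assumed), its share is (d²/4)/(d²/4 + 1.7²). That is 0 for d = 0, 0.25/3.14 = 8% for d = 1, and 0.5625/3.4525 = 16% for d = 1.5.

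**4. Validity.** A simulation (240 participants, 3,000 replicates, assumed regional shares, SD 1.45, effect of 0.5 items) compared an unadjusted t-test on the score with a linear model containing region and topic.

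| Allocation within cells | R² | Type I error, unadjusted / adjusted | Power, unadjusted / adjusted |
|---|---|---|---|
| Simple | 0.05 | 0.046 / 0.044 | 0.76 / 0.76 |
| Simple | 0.15 | 0.053 / 0.052 | 0.76 / 0.81 |
| Simple | 0.30 | 0.052 / 0.047 | 0.76 / 0.89 |
| Blocked | 0.05 | 0.050 / 0.054 | 0.76 / 0.77 |
| Blocked | 0.15 | 0.029 / 0.047 | 0.77 / 0.81 |
| Blocked | 0.30 | 0.019 / 0.047 | 0.79 / 0.89 |

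Under blocking at R² = 0.30 the estimates themselves vary almost equally (SD 0.158 unadjusted, 0.156 adjusted, with the effect present). There the loss lies in a standard error that is too large, not in the estimate. The simulation uses a mean score. The same reasoning applies to a standardised risk difference, but its R² would be that of the binary outcome.

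**The case against.** The strongest reply is that nothing here is invalid. A named, unadjusted test in a 1:1 randomised trial is defensible, and a condensed article often leaves model terms to a fuller document. The first half stands: the working shows no inflation of type I error. The second half does not dispose of the point, because the article names the primary test and states the optional adjustment rule. These are stated choices that can be improved, not details left out.

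A reader might infer more than the documents support, in five ways.

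- **That topic determines the score by construction.** The article says that the questions differ, not that their difficulty does. The survey template is shared and was pilot tested. Topic is plausibly prognostic; its strength is unknown.
- **That the unknown algorithm leaves damaging imbalance.** Not knowing the algorithm does not show that blocking is absent, and the stated purpose of stratification is only an equal chance within region. Even without blocking, a 20-person region has a 26% chance of a 13:7 or worse split, but 13:7 shifts that region's share by 6/120 = 5 points. A full one-item regional difference would then move the estimate by 0.05 items, against a standard error of 1.7×√(2/120) = 0.22. The unadjusted interval already allows for this.
- **That the adjustment decision is wholly driven by the data.** The primary comparison is named, the optional adjustment is not said to replace it, and analysts are blinded, with interpretation agreed under group A and B labels. This limits choosing by direction of effect. It does not stop a choice between two results after seeing both.
- **That topic, literacy and proficiency are neglected.** All three are named subgroups. A subgroup or interaction look, however, does not restore precision to the main comparison.
- **That the proficiency and literacy questions must be moved ahead of the allocated document.** The article does not fix where they sit in the survey, and recruitment began on May 26, 2022. No change to the survey follows from this point.

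**Conclusion.** The point holds as one of efficiency and prespecification, not of validity. The primary comparison ignores the two factors within which format is randomised, and the covariate rule has no trigger. The unadjusted test is sound under simple allocation and conservative if allocation is balanced within cells. The algorithm is not known, so an adjusted analysis is the choice that performs properly in both cases.

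The size cannot be computed from the documents. It is about a fraction R² of the information: 2% to 30% over the assumed range, and close to nothing if region and topic barely predict understanding. It carries more weight because two-sided power at the planned 240 is near 70% rather than 80%. The change is worth making because it costs so little, not because the loss is known to be large.

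**What to change.** - **Primary analysis.** State that formats are compared for understanding with adjustment for topic and region. Merge sparse regions by a rule set without looking at arm.
- **Effect measure.** Keep the stated risk difference through a stratified or standardised estimate, or say openly that a mean-score difference is used instead. The choice needs stating because the sample size section refers to a t-test while the analysis section names a chi-square test.
- **Secondary outcomes.** Use the same terms for those compared between arms.
- **Covariates.** Replace the optional wording in Selection criteria with a fixed statement: English proficiency and health literacy are either both in that model or used only in a named sensitivity analysis.
- **Reporting.** Show the unadjusted result as supportive.

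This should be recorded as a dated amendment before the group labels are revealed. Region and topic are recorded at allocation, and the other two variables are already planned for collection. The cost is therefore wording, slightly more analysis work and the merging rule.
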